#### **Clinical Relevance:**

If findings of the retrospective analysis of BASKET/BASKET-LATE are verified by the prospective BASKET-PROVE and BASKET-PROVE II trials, then 1st generation DES may no longer be justified in large native vessel stenting. This would reduce the late harm which includes late cardiac death, which is most relevant in view of the >6 million DES implanted per year worldwide today. In addition, it would reduce costs considerably due to the much lower price of BMS vs. DES. If, however, findings do not confirm results of BASKET-LATE then the “late harm” observed there was a “chance” finding and no longer relevant, or to a much lesser degree than postulated in BASKET-LATE. If findings differ between different stent types the results will help define the most safe and effective stent type to treat patients with the need for large vessel stenting. In addition, results of the study will help to understand the mechanisms of late stent thrombosis: if late clinical events related to late stent thrombosis do no longer or to a lesser extent occur with newest generation DES with a bioabsorbable polymer, then late stent thrombosis is most likely due to the polymer and not to the drug or drug-dose used. By the historical comparison of the XienceV® stent-arms of BASKET-PROVEII with BASKET-PROVE, the analysis will provide also the unique chance to test the performance of an up-to-date DES with a dual antiplatelet therapy with Prasugrel versus Clopidogrel in an unselected real-world population. – Thus, these findings should have major impact on the current use of coronary stents and our understanding of possible reasons for late stent thrombosis.

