It suggested that patients with small vessel (<3,0 mm) and bypass graft stenting had a highly significant benefit of DES, not only in reduction of target vessel revascularization (TVR), but also in a reduced rate of cardiac death/non-fatal MI. In contrast, data suggested that patients with large native vessel stenting do not seem to benefit from DES and may even have late harm (see Fig.). These findings were confirmed after 36 months (4) and are in accordance with earlier retrospective analyses from different trials showing a particular benefit of DES in small vessels or long lesions (7-11), diabetes mellitus (12-14) and bypass graft stenting (15,16).

In order to prove this hypothesis, BASKET-PROVE (Evaluation of late clinical events after drug-eluting versus bare-metal stents in patients at risk: BASel Stent Kosten Effektivitäts Trial – PROspective Validation Examination) was initiated in 11 centres in Switzerland, Austria, Denmark and Italy in 2007 (17). In this trial a total of 2324 patients in need for large (>3mm stents only) native vessel stenting only were randomised 1:1:1 to either treatment with Cypher-Select® (standard 1st generation DES) versus Vision® (3rd generation cobalt-chromium BMS) versus XienceV® (DES with a lower dose of a “limus” drug, i.e. Everolimus). The results of the primary endpoint (freedom of combination of cardiac death and non-fatal-MI) will be available by summer 2010.

[figure not shown][figure not shown][figure not shown][figure not shown][figure not shown][figure not shown]

Stents <3.0mm or bypass PCI  
n=268 (32%)

Stents ≥3.0mm and no bypasses  
n=558 (68%)

Comparison of bare-metal stents (BMS; blue dotted line) and drug-eluting stents (DES; red continuous line) regarding cardiac survival free of non-fatal myocardial infarction (MI; top), cumulative rate of non-infarct related target vessel revascularisation (TVR; middle), and survival free of major adverse cardiac events (MACE; bottom) in patients treated with small stents <3mm only or with PCI in bypass grafts (left side) and in patients treated with large stents ≥3mm in native vessels (right side).

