## 2. AIMS

These recent findings and analyses are the basis for two relevant questions which will be addressed prospectively in BASKET-PROVE II.

The primary aim will be:

To assess and compare the 24 month safety (cardiac death/MI) of a new type of BMS with new types of DES in patients at low risk of restenosis, i.e. receiving stents of  $\geq 3,0$ mm diameter only, on the background of contemporary antiplatelet therapy.

The new BMS, with thin cobalt-chromium struts and a biocompatible coating (Prokinetik®), will be compared (in a 1:2 randomisation) to two new DES:

- the most widely used 2nd generation DES with a durable polymer and a low dose - limus drug (XienceV®), which was already used in BASKET-PROVE ),
- a DES with a biodegradable polymer and a -limus drug (biolimus) (Nobori®)

The antiplatelet regime will be Aspirin 100mg and Prasugrel 10mg daily for all patients. Based on current recommendations, this will be given for 1 month after BMS in stable patients and for 12 months after DES implantation and after BMS implantation in patients with ACS.

The secondary aims will be:

- A. To compare the efficacy of BMS vs. DES and then the combined endpoint of safety and efficacy of the primary comparison (BMS vs. DES)
- B. To compare safety and efficacy of each of the new DES to that of the BMS, i.e. XienceV® vs Prokinetik® and Nobori® vs Prokinetik® (both, randomized 1:1)
- C. To compare safety and efficacy of the two new DES, i.e. XienceV® vs. Nobori®

There will be also the possibility to compare findings from BASKET-PROVE II with those of the predecessor study BASKET-PROVE. This will have the following additional secondary aims:

D. To compare safety and efficacy of the earlier BMS strategy (Vision® stent with 12 month clopidogrel), as a historical control, with the new BMS strategy (Prokinetik® stent with 1 month Prasugrel in elective patients and 12 months in patients with ACS)

E. To compare safety and efficacy of the the XienceV® stent in similar patient groups (same indications/exclusions, similar sample size) receiving an antiplatelet therapy of 12 month Clopidogrel (BASKET-PROVE) vs. those receiving 12 month Prasugrel (BASKET-PROVE II) in a "historical" control analysis, evaluating also bleeding rates and "net clinical benefit"

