## **10. Data handling and Analyses**

Data management will be based on experience in other large multicenter trials (17,30). Thus, an internet-based electronic CRF will be used for data management. A secure website, accessible by password only, will be provided for data entry. Data will be stored centrally using an SQL-database. Quality of data will be assured by regular on-site monitoring visits, comparing data entered in CRFs with source documents. After monitoring, changes in CRF will be done electronically and only be possible by monitors and study coordination.

The following data will be recorded, in analogy to BASKET-PROVE I:

- Patient history and demographics
- CAD risk factors
- Comorbidities
- Indication for PCI
- Baseline angiographic and procedural characteristics
- Relevant data of stent use and concomitant drug use
- Serious adverse events during follow-up

- Events during follow-up (i.e. all hospitalisations, all coronary interventions, all bleeding, death)
- EQ-5D

For the statistical analysis, the data will be extracted from this database and transferred to and analysed in the commercially available statistical package SPSS v.15.0.

Bivariable comparisons of the DES group with the BMS group will be done using Fisher's exact test for proportions and the Mann-Whitney U-test, for continuous variables. P-values for the comparisons of each of the DES groups to the BMS group will be adjusted using the Bonferroni-Holm method if multiple comparisons of proportions or the Dunnett-Hsu if multiple comparisons of survival curves are performed. Time to event will be evaluated both by Kaplan Meier statistics and multivariable Cox-regression analysis taking into account further influential variables.

Historical comparisons of net clinical benefits will be only of descriptive character.

A priori, missing values will not be imputed. Losses to follow-up will be incorporated since survival analysis will be performed. If outliers values are observed, each will be examined. If it is thought that their cause is of clinical nature, they would be kept in the analysis, otherwise they will be set to missing.

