## **13. Time plan**

Approval of the protocol: Summer 2009

|                                |                                                                                             |
|--------------------------------|---------------------------------------------------------------------------------------------|
| Ethical approval:              | Autumn 2009                                                                                 |
| Start of study:                | January 2010 (Basel; other centres as soon as ethical approval is available at each centre) |
| Inclusion completed:           | Spring 2011                                                                                 |
| Last follow-up completed:      | Spring 2013 (24months)
Spring 2015 (60 months)                                           |
| First presentation of results: | ESC 2013                                                                                    |

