## **15. Clinical Relevance**

If findings of the retrospective analysis of BASKET/BASKET-LATE (12) are verified by the prospective BASKET-PROVE and BASKET-PROVE II trials, then the 1st generation DES may no longer be used for large native vessel stenting. This would reduce the late harm related to late stent thrombosis which includes late cardiac death, which is most relevant in view of the >6 million DES implanted per year worldwide today. In addition, it would reduce costs considerably due to the much lower price of BMS vs. DES. If, however, findings do not confirm results of BASKET-LATE then the “late harm” observed there was a “chance” finding and not relevant further, or to a much lesser degree than postulated in BASKET-LATE. If findings differ between different stent types, results will help define the most safe and effective stent type to treat patients in need for large vessel stenting. In addition, results of the study will help to understand mechanisms of late stent thrombosis: if

late clinical events related to late stent thrombosis do no longer or to a lesser extent occur with newest generation DES with a bioabsorbable polymer, then late stent thrombosis is most likely due to the polymer and not to the drug or drug-dose used. By the historical comparison of the XienceV® stent-arms of BASKET-PROVEII with BASKET-PROVE, the analysis will provide also the unique chance to test the performance of the most widely used DES with dual antiplatelet therapy based on Prasugrel versus Clopidogrel in an unselected real-world population. – Thus, these findings should have major impact on the current use of coronary stents and our understanding of possible reasons for late stent thrombosis.

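### Among the historical comparisons only net clinical benefit is made descriptive, yet the relevance sections speak of testing prasugrel against clopidogrel, which two non-concurrent trials cannot do

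*Protocol*

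**What the plan says.** Section 2 lists two additional secondary aims that use the predecessor trial BASKET-PROVE.

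- **Aim D** sets the old bare-metal strategy against the new one: "To compare safety and efficacy of the earlier BMS strategy (Vision® stent with 12 month clopidogrel), as a historical control".
- **Aim E** sets the XienceV arms of the two trials against each other, for safety and efficacy, with patients "receiving an antiplatelet therapy of 12 month Clopidogrel (BASKET-PROVE) vs. those receiving 12 month Prasugrel (BASKET-PROVE II". It adds bleeding rates and net clinical benefit.

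Section 10 has one sentence on how such comparisons are to be treated: "Historical comparisons of net clinical benefits will be only of descriptive character". Section 8 defines net clinical benefit as the primary end-point plus bleeding.

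The relevance text uses other language. The synopsis calls the XienceV contrast a "unique chance to test the performance of an up-to-date DES with a dual antiplatelet therapy with Prasugrel versus Clopidogrel". Section 15 calls it a "unique chance to test the performance of the most widely used DES with dual antiplatelet therapy based on Prasugrel versus Clopidogrel". Both go on to expect a major impact from the trial's findings.

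On timing, Section 1 says that BASKET-PROVE "was initiated in 11 centres in Switzerland, Austria, Denmark and Italy in 2007". Section 13 plans the start of the present trial for "January 2010 (Basel; other centres as soon as ethical approval is available at each centre").

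**The concern.** The descriptive rule is narrower than the aims it should govern. Read literally, it covers one composite. It leaves out cardiac death/MI, revascularisation and stent thrombosis in both historical aims, and bleeding taken alone in aim E. Someone who follows Section 10 to the letter could report a cross-trial difference in any of these as a finding, and the relevance sections invite that by calling the contrast a test.

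What is at stake is the interpretation of aim E. If background rates of death or infarction fell between the two recruitment periods, the fall would appear as a benefit of prasugrel. If they rose, a real benefit could be hidden. The data offer no means of telling these apart from a drug effect.

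**Working it through.** **1. What changes between the trials**

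| Contrast | Stent | Drug | Duration | Period |
|---|---|---|---|---|
| Aim E (XienceV vs XienceV) | same | clopidogrel to prasugrel | 12 months in both | 2007 start vs 2010 planned |
| Aim D (Vision vs Prokinetik) | changes | clopidogrel to prasugrel | 12 months to 1 month in elective patients; 12 months in both for ACS | 2007 start vs 2010 planned |

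BASKET-PROVE used Cypher, Vision and XienceV on clopidogrel. The present trial uses Prokinetik, XienceV and Nobori on prasugrel. XienceV is the only common stent, and its drug changes. No arm holds stent and drug fixed while only the period moves, so a period effect can be neither estimated nor removed.

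**2. What the plan's own figures cover**

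Section 9 gives 753 versus 1506 patients, 6.0% versus 10.5%, two-sided 0.05 and power above 90%. This reproduces: power is 95.6% by normal approximation and 95.4% by Fisher's exact test. For each DES against BMS at alpha 0.027, Fisher power is 81.5% with 753 per arm, against a stated 80%. Two tests at 0.027 with correlation 0.5 give a familywise level of 0.0501. All of this concerns DES against BMS within the trial. Neither a sample size, nor an alpha, nor a power is stated for a historical contrast, so there is no planned figure to reproduce for it.

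**3. Illustration of the bias**

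Inputs:
- Historical arm: Section 1 reports "a total of 2324 patients in need for large (>3mm stents only) native vessel stenting only were randomised 1:1:1", so 2324/3 ≈ 775.
- Present XienceV arm: 1506/2 = 753 (Section 9).
- Base rates: 6.0% and 10.5% (Section 9).
- Drug effect: zero.
- Drift in event rate between the trials: **assumed**, 0 to 30% relative. The protocol gives no value.

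With d = p1 − p2, pooled rate p̄, s0 = √[p̄(1−p̄)(1/n1+1/n2)] and s1 = √[p1(1−p1)/n1 + p2(1−p2)/n2], the chance of a significant two-sided 5% result is Φ((d − 1.96·s0)/s1) + Φ((−d − 1.96·s0)/s1).

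- 6.0% falling by 20% to 4.8%: d = 0.0120, p̄ = 0.0541, s0 = 0.01157, s1 = 0.01155. First term Φ(−0.92) = 0.178, second term 0.001. Total **17.9%**.
- 10.5% falling by 20% to 8.4%: d = 0.0210, p̄ = 0.0947, s0 = 0.01498, s1 = 0.01495. First term Φ(−0.56) = 0.288, second term below 0.001. Total **28.8%**.

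| Assumed relative fall | Base 6.0%: normal / Fisher | Base 10.5%: normal / Fisher |
|---|---|---|
| 0% | 5.0% / 4.4% | 5.0% / 4.5% |
| 10% | 8.0% / 6.8% | 10.5% / 9.4% |
| 20% | 17.9% / 15.8% | 28.8% / 27.0% |
| 30% | 35.8% / 33.1% | 57.8% / 56.3% |

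With a 20% fall and no drug effect, the relative risk being estimated is 0.80 at any sample size. A stricter alpha or a larger trial would not move it, and a confidence interval would be centred on the wrong value.

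**The case against.** The strongest reply is that the protocol prescribes no historical test at all. In Section 10 the Fisher and Mann-Whitney comparisons are stated for the DES group against the BMS group, and the Bonferroni-Holm and Dunnett-Hsu adjustments for each DES against BMS. The 0.05 and 0.027 levels in Section 9 have the same scope. This stands. A reader might infer that historical safety and efficacy fall under those testing rules, but the text does not support it. Only the sentence on Kaplan-Meier and Cox analysis is unscoped, and it sets no alpha.

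It can also be said that the non-concurrent nature is disclosed. Section 2 presents these aims as a possibility and labels them historical, and the word 'test' occurs only in relevance prose, as a chance. That also stands: the wording is not a promise of a superiority claim. Nor does Section 2 give bleeding and net clinical benefit to aim D; they belong to aim E alone.

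Third, net clinical benefit contains cardiac death/MI, which is the protocol's safety outcome, so the composite that weighs ischaemic benefit against bleeding is already descriptive. This stands only in part. The components taken separately, and revascularisation, remain unnamed.

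Finally, reporting details for secondary historical analyses are commonly left to the SAP. That is so, but here the protocol itself writes a rule, writes it too narrowly for its own aims, and uses contrary language in two other places. The sponsor may well have meant the sentence to cover every historical comparison; if so, the edit only states that intention.

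**Conclusion.** The point holds as a mismatch between aims, rule and claim. Net clinical benefit is the only historical comparison restricted to description, and the relevance sections credit the XienceV contrast with a property that the design lacks. The documents alone establish that drug and period are confounded in aim E, and stent as well in aim D, with treatment duration too in elective patients.

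A reader might infer that the fault is a missing alpha. It is not: the fault is bias, which no alpha allocation would cure. A reader might also take 18% to 29% (16% to 27% with Fisher) as a forecast. It is an illustration that rests on an assumed 20% fall, on no drug effect and on Section 9's rates applied to the XienceV arms. Without drift the nominal level holds.

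The primary comparison and aims A to C are randomised and unaffected. Severity is minor to moderate.

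**What to change.** In Section 10, replace the sentence on historical comparisons with:

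> All historical comparisons (aim D: safety, efficacy; aim E: safety, efficacy, bleeding, net clinical benefit) are descriptive, reported as estimates with 95% confidence intervals and without a claim of superiority.

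In the Clinical Relevance text of the synopsis and in Section 15, replace 'test' by 'describe' and add that drug and calendar period cannot be separated in this comparison. That statement is needed alongside the intervals, because an interval does not show the bias. Whether p-values are also left out is a reporting choice that the SAP can settle.

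The cost is wording in three places. No patients, data or analyses are added. The sponsor gives up only a claim that the design could not support.

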##### **Statistics:**

A sample size of 800 patients/stent type (753 plus compensation for a withdrawal rate of 5 to 6%) would provide a power of more than 90% to detect, at an alpha level of 0.05 in a two

tailed test, a significant difference between the BMS group and the DES group. This sample size will also allow to detect a significant difference between the BMS and each of the DES groups with a power of 80% at an alpha level of 0.027.

Intention to treat analysis: bivariable group comparisons will be first performed, then time to event will be evaluated both by Kaplan Meier statistics and Cox-regression analysis taking into account influential factors.

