## 5. Follow-up

- Follow-up will be clinical with no “routine” follow-up angiography allowed (follow-up angiography only for relevant new symptoms!)

After 24 , 36 and 60 months a structured questionnaire will be sent to all study patients regarding clinical events (1st, 2nd endpoints) as well as drugs used. In addition, quality of life will be assessed using the self-administered EQ-5D questionnaire, which consists of a self classifier and a visual analogue scale, at baseline and after 24, 36 and 60 months (26,27). All events will be documented based on hospital and/or private physician charts/discharge letters.

- A separate registry will be conducted including all patients treated with PCI during the time of randomisation but not included in the main trial.

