## 9. Sample Size calculation

In the 558 patients of BASKET/BASKET-LATE with treatment of large native vessels, cardiac deaths and non-fatal MIs were seen in 6% of BMS compared to 11.2% of DES treated patients ( $p=0.05$ ) after a follow-up of 18 months. Based on a slightly more conservative assumption (i.e. 6.0 vs. 10.5% after follow-up of 24 months) and on the design of the proposed study, a total of 753 patients for the BMS group and a total of 1506 patients for the DES group (which includes the XienceV® and Nobori® groups) would have to be included to reject the null hypothesis that the event rates for the DES and BMS groups are equal at an alpha level=0.05 in a two-tailed test with probability of more than 90% (power). In view of an expected withdrawal rate of 5-6% and the 2:1 randomization, we plan to enroll 3x800 patients into the study or a total of 2400 patients; i.e. we could still detect a relative difference of 22% between BMS and DES at an alpha level of .027 with a power of 70% if the BMS rate stays the same, and with a slighter higher power an an alpha level of .05 if the BMS rate would be 5.5% instead of 6%. To address the second aim (comparison of BMS with each of the two DES) within BASKET-PROVE II, the sample size of 800 patients per stent group will allow to reject the null hypotheses that the event rates for each of the DES and the BMS are equal at an alpha level of 0.027 in a two-tailed test with a power of 80%. A simulation showed that a nominal alpha of 0.027 is appropriate to adjust for the duplicity of testing in the following setting: if three groups of equal size are compared with respect to the relative frequency of a certain outcome, the z-standardized differences ( $p_2-p_1$ ) and ( $p_3-p_1$ ) follow a 2-dimensional normal

distribution with variance 1 and covariance 0.5 under the null hypothesis. The Fisher's exact test will be used to evaluate the above hypotheses.

If we assume a total inclusion rate of 170 patients per month as in BASKET-PROVE by all participating centres, we should finish inclusion within 13-15 months. If results of BASKET-PROVE should differ markedly from these assumptions, i.e. difference in rates in cardiac death/MI of BMS patients vs. XienceV® patients <3.0% or >5.0%, then these sample size considerations will have to be reassessed.

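### Applied to EQ-5D, the protocol's generic rule for continuous variables leaves the baseline score unused and compares only survivors who return the questionnaire

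*Protocol*

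**What the plan says.** Section 5 (Follow-up) of the protocol says that "quality of life will be assessed using the self-administered EQ-5D questionnaire", with a descriptive part and a visual analogue scale, "at baseline and after 24, 36 and 60 months". Section 10 (Data handling and Analyses) lists EQ-5D among the data to be recorded.

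Section 10 then gives rules that are not tied to any one variable:

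- DES and BMS are compared by Fisher's exact test for proportions and by "the Mann-Whitney U-test, for continuous variables".
- "A priori, missing values will not be imputed".
- "Losses to follow-up will be incorporated since survival analysis will be performed".
- Adjustment for other variables is mentioned only for Cox regression.

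The synopsis (Statistics) announces: "Intention to treat analysis: bivariable group comparisons will be first performed". Section 9 (Sample Size calculation) assumes cardiac death/MI rates of "6.0 vs. 10.5% after follow-up of 24 months" for BMS and DES.

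EQ-5D appears neither in the aims (section 2) nor in the endpoint list (section 8). The protocol has no sentence on how EQ-5D is analysed, on patients who die before a questionnaire is due, or on any use of the baseline score.

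**The concern.** EQ-5D is the only scored outcome that the protocol names at follow-up, so the general rule for continuous variables is the only stated rule that can govern it. Two consequences follow if that rule is used as written.

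First, a two-sample test on follow-up scores takes no account of the baseline EQ-5D that section 5 already collects. Precision is given up although the data exist.

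Second, a self-administered form cannot be returned by a patient who has died. Without imputation, the comparison is confined to survivors who respond. The remedy that section 10 offers for incomplete follow-up, survival analysis, does not act on a score at a fixed time. The plan assumes more cardiac death/MI with DES, so the missing patients may be unequal by arm. The EQ-5D result would then describe quality of life among survivors, and nothing in the text tells the reader so.

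**Working it through.** **Inputs from the protocol (section 9).** Assumed 24-month cardiac death/MI 6.0% (BMS) and 10.5% (DES); 753 and 1506 patients; two-sided alpha 0.05. The protocol gives no figure for EQ-5D.

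**The plan's own figure.** The pooled rate is (6.0 + 2 × 10.5)/3 = 9.0%. The standard error is √[0.09 × 0.91 × (1/753 + 1/1506)] = 0.01277 under the null, and √(0.06 × 0.94/753 + 0.105 × 0.895/1506) = 0.01172 under the alternative. Power = Φ[(0.045 − 1.96 × 0.01277)/0.01172] = Φ(1.70) = 95.6%, which agrees with the stated power of more than 90%. The rates and arm sizes used below are therefore consistent with the plan.

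**Inputs assumed, because the documents do not give them.** Share f of the primary events that are fatal; mean and SD of EQ-5D in survivors; correlation r between baseline and follow-up EQ-5D.

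**Step 1: gain from using baseline.** With linear ANCOVA the residual variance is multiplied by 1 − r², which is equivalent to a sample larger by 1/(1 − r²) − 1. A comparison with 80% power unadjusted would have power Φ[(1.96 + 0.842)/√(1 − r²) − 1.96].

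| r (assumed) | 1 − r² | Equivalent extra patients | 80% power becomes |
|---|---|---|---|
| 0.3 | 0.91 | 10% | 84% |
| 0.4 | 0.84 | 19% | 86% |
| 0.5 | 0.75 | 33% | 90% |
| 0.6 | 0.64 | 56% | 94% |

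The 80% is only a reference point, as the protocol sets no power target for EQ-5D. The formula is for linear ANCOVA and was not evaluated for a rank-based version. Section 4 enrols emergency patients around the procedure, and their baseline score may predict later scores less well.

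**Step 2: unequal loss through death at 24 months.** Expected deaths among primary events are 753 × 0.06f (BMS) and 1506 × 0.105f (DES). At f = 1/2 this is 22.6 and 79.1, or 3.0% against 5.25% of each arm. At f = 1 it is 45.2 and 158.1. Non-cardiac deaths are outside these rates, and no rates are given for 36 or 60 months.

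**Step 3: what a survivors-only test would not reflect.** Suppose survivors score alike in both arms and deaths take the worst rank. The probability that a DES patient does better than a BMS patient is then 0.5 − 0.5 × (0.105f − 0.06f) = 0.5 − 0.0225f. The standard error is √[(2259 + 1)/(12 × 753 × 1506)] = 0.0129.

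| f (assumed) | Probability | Shift in standard errors |
|---|---|---|
| 1/3 | 0.4925 | 0.58 |
| 1/2 | 0.4887 | 0.87 |
| 2/3 | 0.4850 | 1.16 |

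A simulation (1,000 runs per setting, survivor mean 0.80, SD 0.20, scores capped at 1, equal arms) gives the same picture. The survivors-only Mann-Whitney test rejects in about 4% to 6% of runs throughout. With deaths at worst rank it rejects in about 8%, 14%, 25% and 42% for f = 25%, 50%, 75% and 100%.

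**Step 4: the index scale, deaths scored 0.** The mean difference is −0.045 × f × (survivor mean). For f = 1/3 with mean 0.70 it is −0.0105; for f = 2/3 with mean 0.85 it is −0.0255. The variance in each arm must include the spread that the zeros add: (1 − p) × 0.20² + p(1 − p) × mean², where p is the death rate. The standard errors are then 0.0101 and 0.0120, so the shifts are 1.0 and 2.1 standard errors.

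**The case against.** The strongest reply is that the protocol specifies no EQ-5D comparison at all. The Mann-Whitney sentence is general and fits baseline characteristics equally well. EQ-5D is not an endpoint, and its detailed analysis belongs in an SAP, which is not at hand. This stands as a limit on the point: the link from rule to EQ-5D is an inference, and the protocol does not contradict itself here. It does not remove the point, because the general rule has no exception and a better method is available from data already collected.

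A Mann-Whitney test on change from baseline would also satisfy the text, so a reader should not infer that the protocol has ruled baseline out. It names no use of it. Change scores would be a poor substitute: with equal variances at both times, their variance relative to the unadjusted score is 2(1 − r), which is 1.4 at r = 0.3 and 0.8 at r = 0.6, against 0.91 and 0.64 for ANCOVA.

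A reader might infer that the plan hides a quality-of-life loss from deaths. The documents do not support that. Cardiac death is in the primary endpoint; its components, non-cardiac death and total death are listed secondary endpoints; and follow-up runs to 60 months. An excess of deaths would be seen beside any EQ-5D result.

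A reader might also infer that worst rank should be the main analysis. Quality of life among survivors, read with mortality, is a legitimate question, and merging death into the score is a debatable choice. Nor does the text class a dead patient's score as missing, so a worst-rank rule could be read as compatible with it.

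**Conclusion.** The point holds as a modest, inexpensive improvement. The only stated rule that can reach EQ-5D is unadjusted and without imputation. Followed literally, it uses no baseline score and compares only survivors who respond, and survival analysis cannot repair that.

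The gain from baseline adjustment is about 10% to 56% in equivalent sample size for linear ANCOVA at r = 0.3 to 0.6, and it may be smaller for a rank version or for emergency patients. The effect of deaths is conditional: 0.6 to 1.2 standard errors on the rank scale and 1.0 to 2.1 on the index scale for fatal shares of one third to two thirds. At those shares a death-inclusive rank test would usually still show no significant difference. All these sizes rest on assumed inputs, and the 6.0% and 10.5% combine cardiac death with non-fatal MI. Nothing can be computed for 36 or 60 months.

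No primary or listed secondary result, sample size or error rate is affected.

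**What to change.** Add to section 10, before results by stent group are seen:

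1. EQ-5D at 24, 36 and 60 months is compared between DES and BMS by ANCOVA, or rank-based ANCOVA, with baseline EQ-5D as covariate. The Mann-Whitney test remains for other continuous variables.
2. The main result is labelled as quality of life among survivors and is shown beside mortality at the same time point.
3. A sensitivity analysis keeps patients who have died in the comparison at worst rank (index value 0). The rule against imputation then covers questionnaires missing in living patients.

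The cost is a few sentences and a little programming. Baseline EQ-5D and deaths are already recorded. The one drawback is that the sensitivity result mixes mortality with quality of life, which is why it should stand next to the survivors' result and not replace it. Fixing the rule in advance also avoids choosing between the two analyses after the data are known, which matters in an open-label trial.
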